**Methods/Design:**

Participants will be adults aged 25–74 years registered with general practices in the East of England, diagnosed with type 2 diabetes, with no history of heart disease, and with a glycated haemoglobin level of ≥6.45 % (47 mmol/mol). Consenting participants will be randomised to one of three arms: usual care control, group self-management only, group self-management plus personalised genetic- and lifestyle-associated risk information. The self-management groups will receive four weekly 2-hour group sessions, focusing on knowledge and information sharing, problem solving, goal setting and action planning to promote medication adherence, healthy eating, and physical activity. Primary outcomes are glycaemic control and CHD risk. Clinical data will be collected from GP records, including HbA1c, weight, body mass index, blood pressure, and HDL and total cholesterol. Self-reported health behaviours, including medication adherence, healthy eating and physical activity, and cognitive outcomes will be assessed by questionnaire. Measures will be taken at baseline, 3 months (questionnaire only), 6 months and 12 months post-baseline.

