### Primary outcomes

*HbA1c.* Change in blood glucose control as measured by glycated haemoglobin (HbA1c) will be recorded from patient’s medical records. HbA1c reflects average plasma glucose concentration over an 8–12-week period and will be collected at baseline and 6 and 12 months post-baseline.

*UKPDS risk.* Ten-year risk of CHD defined as fatal, and non-fatal, MI will also be calculated at baseline and 6 and 12 months post-baseline using the UKPDS risk engine (v2.0) [28]. UKPDS is a risk calculator specifically for people with type 2 diabetes. Percentage risk is calculated from participants’ age, years since diabetes diagnosis, presence of atrial fibrillation, reported smoking behaviour, sex, ethnicity, HbA1c, systolic BP, and total and HDL cholesterol.

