### Power calculation

A clinically important change in HbA1c level of 12.5 % (SD 15.5 %) was identified from a Health Technology Assessment of blood glucose monitoring devices [35] over a period of 18 months. This represents a reduction in HbA1c (%) from 8 to 7 or from 9 to 7.9. As the current study has a shorter follow-up, we base our sample size calculations on a conservative change that would be clinically achievable in this time frame: an HbA1c change of 6.25 % representing a reduction from an HbA1c (%) of 8 to 7.5 or from 9 to 8.44 (this represents a change from 63.9 mmol/ml to 59.9 mmol/ml; and 74.9 mmol/ml to 69.4 mmol/ml).

The expected 6.25 % change in HbA1c (SD = 15 %) represents an effect size of d = 0.40, a small to moderate effect size (d = 0.2 – small, 0.5 – medium and 0.8 – large effect); equivalent to effect size f = 0.2 in G*Power [36] calculated for repeated measures, between-subjects analysis of variance (ANOVA) analyses. Based on the current design (three groups, four measurement points), alpha = 0.05, power = 80 %, f = 0.20 and a correlation between measurement points of 0.70, G*Power indicates a total sample size of 192. With an expected attrition rate of 20 %, a sample size of 240 (80 per study arm) will be sought.

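### The HbA1c power calculation uses a two-group effect-size conversion and one measurement too many; on its own test, power for d = 0.40 at N = 192 is about 61 % to 74 %, not 80 %

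*Protocol article*

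**What the plan says.** The Power calculation section of the protocol article sets the target difference on HbA1c: "The expected 6.25 % change in HbA1c (SD = 15 %) represents an effect size of d = 0.40". It calls this "equivalent to effect size f = 0.2 in G*Power [36] calculated for repeated measures, between-subjects analysis of variance (ANOVA) analyses". The inputs are then "Based on the current design (three groups, four measurement points), alpha = 0.05, power = 80 %, f = 0.20", with "a correlation between measurement points of 0.70, G*Power indicates a total sample size of 192". Attrition is added last: "With an expected attrition rate of 20 %, a sample size of 240 (80 per study arm) will be sought".

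Three other places describe the design differently for HbA1c:
- The abstract (Methods/Design) says "Measures will be taken at baseline, 3 months (questionnaire only), 6 months and 12 months post-baseline".
- Primary outcomes says that HbA1c "will be collected at baseline and 6 and 12 months post-baseline".
- Main analyses plans a three-group by three-time mixed ANCOVA for HbA1c and CHD risk, with Sidak-corrected post hoc comparisons, or a multi-level model in its place.

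Randomisation and blinding fixes 1:1:1 allocation.

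**The concern.** Cohen's f is the standard deviation of the group means divided by the within-group SD. It equals d/2 only when there are two equal groups. With three equal arms, the same largest difference gives a smaller f, because the third mean lies at or between the extremes. Entering f = 0.20 with three groups therefore assumes a larger separation than the d = 0.40 the protocol says it is powered for. The count of four measurement points also contradicts the HbA1c schedule given elsewhere in the article.

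Readers will judge a null result, particularly for adding risk information to self-management, against the claim of 80 % power for a 6.25 % HbA1c difference. If that claim is not supported, a null result may be taken as stronger evidence of no effect than it is.

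**Working it through.** **Inputs.** From Power calculation: change 6.25 %, SD 15 %, d = 0.40, f = 0.20, 3 groups, m = 4, alpha 0.05, rho = 0.70, N = 192, attrition 20 %. From Primary outcomes and the abstract: m = 3 for HbA1c. From Randomisation and blinding: equal arms.

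**Formula.** For the G*Power option the protocol names (repeated measures, between-subjects F test), lambda = N f² m / (1 + (m − 1) rho), with degrees of freedom 2 and N − 3.

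**Step 1: reproduce the stated figure.** lambda = 192 × 0.04 × 4 / (1 + 3 × 0.70) = 30.72 / 3.1 = 9.91. Power is 80.5 %, and 192 is the smallest N in equal arms that reaches 80 %. With attrition, 192 / 0.80 = 240. The arithmetic is right, so the inputs used are known.

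**Step 2: f for three equal arms with largest difference d.**
- Two arms equal, one apart (the maximum): f = d √2 / 3 = 0.40 × 0.4714 = 0.189.
- Third arm midway (the minimum): f = d / √6 = 0.40 / 2.449 = 0.163.

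With the unrounded d = 6.25/15 = 0.417, these become 0.196 and 0.170. Reaching f = 0.20 needs d between 0.20 × 3/√2 = 0.424 and 0.20 × √6 = 0.490.

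**Step 3: power at N = 192 on the same test.**

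| Change made | f | m | Power | N for 80 % |
|---|---|---|---|---|
| None | 0.200 | 4 | 80.5 % | 192 |
| Measurements only | 0.200 | 3 | 79.2 % | 198 |
| Conversion only | 0.189 | 4 | 75.4 % | 216 |
| Conversion only | 0.163 | 4 | 62.1 % | 285 |
| Both | 0.189 | 3 | 74.0 % | 222 |
| Both | 0.163 | 3 | 60.6 % | 294 |
| Both, d = 0.417 | 0.196 | 3 | 77.6 % | 204 |
| Both, d = 0.417 | 0.170 | 3 | 64.4 % | 270 |

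The measurement count alone costs 80.5 − 79.2 = 1.3 points. The rest is the conversion.

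**Step 4: what 80 % at N = 192 and m = 3 does cover.** Solving for f gives 0.202, so the largest difference is 0.202 × 3/√2 = 0.43 (two arms equal) to 0.202 × √6 = 0.49 (third arm midway).

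**Step 5: a pairwise contrast closer to the trial's question.** Assumptions: 64 completers per arm, baseline-adjusted mean of the 6- and 12-month values, rho = 0.70 between all pairs of visits, effect present at both follow-ups. In single-value SD units the residual variance is (1 + 0.70)/2 − 0.70² = 0.36, so the residual SD is 0.60. The Sidak level for three comparisons is 1 − 0.95^(1/3) = 0.017.
- SD is of a single value: standardised effect 0.40/0.60 = 0.667; power about 91 % (96 % at 0.05).
- SD is of change: the SD of change is √(2 × 0.30) = 0.775 single-value units, so the standardised effect is 0.40 × 0.775/0.60 = 0.516; power about 69 % (83 % at 0.05).

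**The case against.** A reader might infer that the trial as designed cannot deliver 80 % power. The documents do not support that. Main analyses plans a 3 x 3 mixed ANCOVA or a multi-level model, and does not name the between-subjects mean over all visits as the confirmatory term. If the SD is of a single value and the effect is present at both follow-ups, a group-by-time test on three measurements has about 77 % to 89 % power at N = 192. An omnibus ANCOVA adjusted for baseline HbA1c has about 93 % to 98 %, although the article does not name baseline HbA1c as a covariate. This objection stands and limits the conclusion to the stated calculation.

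Lower figures are also tempting. If the confirmatory test were the main effect averaged over baseline as well, the effect would shrink by 2/3 and power would be about 30 % to 39 %. An unadjusted pairwise test on a single change score gives about 44 % at the Sidak level. Each depends on a test the protocol does not commit to, and neither should be quoted as the trial's power.

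It can also be said that the unrounded d = 0.417 gives f = 0.196 when two arms are equal, which rounds to 0.2, leaving a shortfall of only 80 − 77.6 = 2.4 points. That is fair for this one pattern of means. The protocol states no pattern, and with the third arm midway, power is still 64.4 %. Finally, the measurement count is close to immaterial numerically; it is a contradiction to correct, not the source of the loss.

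**Conclusion.** The calculation is wrong as written. Its arithmetic reproduces, but f = d/2 does not apply to three arms, and four measurements do not match the HbA1c schedule. On the protocol's own test, with rho = 0.70 and 192 completers, power for a largest difference of d = 0.40 is about 61 % to 74 %, or 64 % to 78 % at d = 0.417. The position within each range depends on where the third arm falls, which the article does not say. No three-arm pattern with either value of d reaches 80 %.

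The finding is that the stated calculation does not support the stated power. Whether the analysis eventually used exceeds or misses 80 % depends mainly on the meaning of the SD and on baseline adjustment, and the article settles neither.

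**What to change.** Keep the target of 240 and rewrite the power paragraph:

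1. Use three measurement points and a three-arm f. Then either restate the power as about 61 % to 78 %, depending on the pattern of means and the SD, or state that 80 % applies to a largest between-arm difference of about d = 0.43 to 0.49.
2. Reconcile the SD of 15 % used for d with the 15.5 % quoted from the source assessment (6.25/15 = 0.417; 6.25/15.5 = 0.403). Say whether it is the SD of change or of a single value.
3. Preferably, also report power for the baseline-adjusted pairwise contrast at the Sidak level with 64 completers per arm: about 91 % if the SD is of a single value and about 69 % if it is of change, with the assumptions stated.

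The cost is one reworded paragraph and no extra participants. On the omnibus test now quoted the figure becomes less favourable; for the pairwise contrast it may be better or worse than 80 %, depending on the SD.

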#### Main analyses

Spearman’s or Pearson’s correlations will determine relationships between variables and chi-squared analyses will be used to compare rates data. For the main group differences and time-based analyses, data will be analysed using intention-to-treat principle and then repeated with per protocol subsamples, for sensitivity analyses. For the main continuous outcome measures (HbA1c and CHD risk data) and secondary outcomes 3 x 3 mixed analysis of covariance (ANCOVA) controlling for existing group differences on key process variables will be conducted for each outcome, with post hoc comparisons using Sidak’s correction. Should the data meet the criteria for multi-level modelling, these analyses will be conducted in lieu of ANCOVA.

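### The HbA1c sample size assumes four measurement points, but both primary outcomes have three; the effect on power is small, and whether 80 % is met depends on which of two stated SDs was meant

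*Protocol article*

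**What the plan says.** The Power calculation section works from HbA1c. It first cites a change of 12.5 % with SD 15.5 % over 18 months, taken from a health technology assessment. It then halves the change for this trial's shorter follow-up and gives a different SD: "The expected 6.25 % change in HbA1c (SD = 15" %. This, it says, "represents an effect size of d = 0.40, a small to moderate effect size", and is "equivalent to effect size f = 0.2 in G*Power" for a repeated-measures, between-subjects ANOVA. The remaining inputs are "Based on the current design (three groups, four measurement points", alpha 0.05, "power = 80 %, f = 0.20" and a correlation of 0.70 between measurement points. The result is 192 in total, raised to 240 (80 per arm) for 20 % attrition.

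The rest of the article gives the primary outcomes a different schedule. Under Primary outcomes, HbA1c "will be collected at baseline and 6 and 12 months post-baseline", and UKPDS risk is calculated at the same three times. The abstract's Methods/Design paragraph says "Measures will be taken at baseline, 3 months (questionnaire only), 6 months and 12 months post-baseline". Under Main analyses, HbA1c and CHD risk are to be analysed by "3 x 3 mixed analysis of covariance (ANCOVA"). The Secondary outcomes section gives the four-time schedule only to the self-reported behavioural, cognitive and psychological measures.

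**The concern.** The calculation is for a laboratory outcome but uses the number of time points of the questionnaires. In the between-subjects test of a repeated-measures design, each extra measurement adds precision to a participant's average. Entering four points therefore credits the trial with an HbA1c value at 3 months that will not be collected. As a result, 192, 240 and 80 % do not describe the outcome and the model that they are meant to support.

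The effect size next to it cannot be traced cleanly either. Two SDs are printed, and the one attached to this trial's expected change does not give the stated d to the precision shown. A reader who wants to know what power the trial has for HbA1c cannot derive one answer from the text.

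**Working it through.** **Inputs.** From Power calculation: f = 0.20, correlation ρ = 0.70, alpha 0.05, k = 3 groups, target power 80 %, attrition 20 %, and m = 4 as entered. From Primary outcomes and Main analyses: m = 3. Arms are equal (1:1:1, Randomisation and blinding), so N is taken in multiples of 3.

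**Formula.** Between-subjects F test in a repeated-measures ANOVA:

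- noncentrality λ = f² × N × m / (1 + (m − 1)ρ)
- degrees of freedom 2 and N − 3
- power = P(noncentral F > 5 % critical value); at N = 192 the critical value is 3.044.

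**Step 1: reproduce the plan (m = 4).**

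- m/(1 + (m − 1)ρ) = 4/(1 + 3 × 0.70) = 4/3.1 = 1.290
- N = 192: λ = 0.04 × 192 × 1.290 = 9.91, power 80.5 %
- N = 189: λ = 9.75, power 79.8 %

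So 192 is the smallest equal-arm total that reaches 80 %, and 192/0.8 = 240. Both stated figures reproduce. The four-point input was therefore really used and is not a slip of wording over a correct calculation.

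**Step 2: change only the number of points (m = 3).**

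- 3/(1 + 2 × 0.70) = 3/2.4 = 1.250
- N = 192: λ = 0.04 × 192 × 1.250 = 9.60, power 79.2 %
- N = 195: λ = 9.75, power 79.8 %
- N = 198: λ = 9.90, power 80.5 %

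Reaching 80 % takes 198 in equal arms (196 if arms may differ), 6 more than stated. Recruited: 198/0.8 = 247.5, so 248, or 249 in equal arms. Put the other way, 240 recruited leaves 198 if attrition is 1 − 198/240 = 17.5 %.

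**Step 3: the two SDs.** As in the plan, f is taken as d/2.

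- SD 15.5 %: d = 6.25/15.5 = 0.403, f = 0.2016
- SD 15 %: d = 6.25/15 = 0.417, f = 0.208

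| f used (m = 3) | Power at N = 192 | Smallest equal-arm N for 80 % |
|---|---|---|
| 0.20 as entered | 79.2 % | 198 |
| 0.2016 (SD 15.5 %) | 79.9 % | 195 |
| 0.208 (SD 15 %) | 82.5 % | 183 |

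Across these rows, the choice of effect size moves the power by 3.3 points (82.5 − 79.2). Changing from four points to three moves it by 1.3 points (80.5 − 79.2, at f = 0.20).

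**The case against.** The strongest reply is that nothing material follows. At a correlation of 0.70 the factor that carries the number of points falls only from 1.290 to 1.250. At f = 0.20 the power ends 0.8 points under target, and the gap is 6 evaluable participants. The correlation is itself an assumption: with three points, 0.65 in place of 0.70 gives 81.0 % at 192. The trial as a whole does have four assessment times, so the description of the design is true of the trial even though it is wrong for the primary outcomes. All of this stands and limits the size of the point. It does not make the input right.

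A reader might go further and infer that the trial falls short of 80 % power on its own inputs. The documents do not support that. The shortfall appears if f is held at the rounded 0.20, or if the SD is 15.5 %. The SD in the sentence that defines this trial's expected change is 15 %, and used unrounded it gives 82.5 % with three points.

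A reader might also infer that 15.5 % must be the intended SD because it gives d = 0.40. That is not shown either. The text attaches 15.5 % to the cited 18-month change and 15 % to this trial's change, and 0.40 could equally be a cautious rounding down of 0.417.

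**Conclusion.** The number of measurement points is wrong for the outcome being sized, and the protocol article contradicts it in its abstract, its outcome definitions and its analysis section. The consequence is small. At the entered f = 0.20 and correlation 0.70, power at 192 is 79.2 % where the four-point calculation gives 80.5 %, and 80 % would need 198 evaluable participants. The SD is stated in two ways, and with three points the power at 192 is 79.9 % or 82.5 % according to which was meant. Whether the 80 % target is met cannot be settled from the text. These figures rest on the plan's own correlation, alpha, group number and step from d to f, and on the between-subjects F test that it names. This is a wrong input and an unreconciled effect size to correct. It is not evidence that the trial is materially underpowered.

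**What to change.** In the Power calculation section:

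1. Replace four measurement points with three (baseline, 6 and 12 months), to agree with Primary outcomes and Main analyses.
2. Say which SD was intended for the 6.25 % change, and give the d and f that follow from it. If f = 0.20 is kept as a deliberate rounding, say so.
3. Restate the power that 192 evaluable participants deliver: about 79 % if f = 0.20 is kept, 79.9 % for SD 15.5 %, or 82.5 % for SD 15 %.

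The cost is one re-run of the routine and a few words of text. The recruitment target of 240 need not change. If the sponsor keeps f = 0.20 and wants a full 80 %, the matching statement is 198 evaluable participants, which 240 recruited supplies at attrition of up to 17.5 %.

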### Analysis

#### Preliminary analyses

Descriptive statistics will be used to assess levels of missing data, the frequency of events, participant characteristics, and the central tendency and dispersion of key variables. If missing data analyses indicate large levels of missing data (>10 % on any variable), multiple imputation using SPSS Markov Chain Monte Carlo procedures (IBM Corp., Armonk, NY, USA) will be implemented to produce 10 imputed datasets. These will each be analysed as specified below; thereafter standard multiple imputation procedures will be used to combine the multiple scalar and multivariate estimates quantities. If missing data levels are lower, a single imputation procedure will be implemented, followed by standard analyses procedures.

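### Ten imputed datasets are valid but few for the 20 % attrition expected; 50 or more would cut the Monte Carlo noise in a follow-up contrast by more than half at almost no cost

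*Protocol article*

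**What the plan says.** The Preliminary analyses section of the protocol article makes the handling of missing data depend on how much is missing. At "large levels of missing data (>10 % on any variable", multiple imputation by Markov chain Monte Carlo in SPSS "will be implemented to produce 10 imputed datasets". Each set is analysed as planned, and "standard multiple imputation procedures will be used to combine" the results. Below that level a single imputation is used. No reason is given for the number 10.

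The Power calculation section states: "With an expected attrition rate of 20 %, a sample size of 240 (80 per study arm) will be sought". The primary outcomes are HbA1c and UKPDS 10-year CHD risk, both at baseline, 6 and 12 months. The Main analyses section plans a 3 x 3 mixed ANCOVA for each, with Sidak-corrected post hoc comparisons, or multi-level models in its place.

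**The concern.** The expected attrition is twice the 10 % trigger, so on the plan's own figure the multiple-imputation branch is the likely route for HbA1c. UKPDS risk takes HbA1c, systolic blood pressure and both cholesterol values as inputs, so it cannot be more complete than HbA1c.

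Pooled results from a finite number of imputations carry random error from the imputation draws. With few imputations and appreciable missing information, that error can move a borderline test statistic across its threshold. The trial is planned at 80 % power for a small-to-moderate effect, with two primary outcomes and three arms, so a borderline contrast is plausible. The seed should have as little say in it as is practical.

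**Working it through.** **1. The plan's own sample size.** The inputs are "alpha = 0.05, power = 80 %, f = 0.20 and a correlation between measurement points of 0.70" with "three groups, four measurement points". For the between-groups repeated-measures test, the noncentrality is N f² m / (1 + (m - 1)ρ) = 192 x 0.04 x 4 / (1 + 3 x 0.70) = 30.72 / 3.1 = 9.91, on 2 and 189 degrees of freedom. Power is 0.805, so 192 is reproduced. 192 / 0.80 = 240, or 80 per arm, is reproduced too. The 20 % is therefore the planning figure for the HbA1c analysis.

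**2. Efficiency of ten imputations.** The FMI is not in the article; I take 0.20, equal to the expected attrition. Relative efficiency is 1 / (1 + 0.20/10) = 0.98.

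**3. Monte Carlo SD of the pooled statistic, M = 10, near z = 1.96.**
- From the estimate: sqrt[(FMI/M) / (1 + FMI/M)] = sqrt(0.020 / 1.020) = 0.140.
- From the pooled standard error: 1.96 x ½ x FMI x sqrt(2/(M - 1)) = 0.196 x 0.471 = 0.092.
- Together: sqrt(0.140² + 0.092²) = 0.168.

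The same formula gives 0.110 at FMI 0.10 and 0.194 at FMI 0.25. With M = 50 and FMI 0.20 it gives 0.075.

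**4. What this does to a p-value at 0.05.** With SD 0.15, z = 1.96 ± 0.30 runs from 1.66 to 2.26, so two-sided p runs from 0.097 to 0.024. Over the FMI range, the 95 % interval for p at M = 10 goes from 0.030-0.081 (FMI 0.10) to 0.019-0.114 (FMI 0.25).

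**5. Simulation.** Settings: 80 per arm, three time points, correlation 0.70, and 20 % per arm lost at random by 12 months, either all before 6 months or half before and half after. Imputation was by proper Bayesian regression, pooling by Rubin's rules with small-sample degrees of freedom, and results were recentred near p = 0.05. Where two values are shown, they are for the two dropout patterns. Columns give the seed-to-seed SD and the 95 % range of p.

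| Contrast | FMI | M = 10: SD; p | M = 50: SD; p |
|---|---|---|---|
| 12-month ANCOVA | 0.205 / 0.190 | 0.176; 0.023-0.111 / 0.166; 0.024-0.106 | 0.076; 0.037-0.069 / 0.076; 0.037-0.068 |
| Change to 12 months | 0.180 / 0.167 | 0.162; 0.025-0.105 / 0.153; 0.026-0.100 | 0.070; 0.038-0.067 / 0.070; 0.038-0.067 |
| Mean of 6 and 12 months, ANCOVA | 0.203 / 0.135 | 0.175; 0.023-0.110 / 0.134; 0.028-0.092 | 0.076; 0.037-0.069 / 0.060; 0.039-0.064 |
| Mean of baseline, 6 and 12 months | 0.047 / 0.030 | 0.074; 0.036-0.070 / 0.058; 0.039-0.065 | 0.032; 0.044-0.057 / 0.026; 0.045-0.056 |

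For the 12-month ANCOVA contrast, 100 imputations give SD 0.053 and p 0.041-0.062.

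**6. How often the seed would change the verdict.** For two independent seeds on the same data, the mean absolute difference in the statistic is 1.128 x SD. The chance that 0.05 falls between the two results is about that difference times the density of the statistic at the threshold. The density is 2 x 0.0584 = 0.117 under the null. At 80 % power it is 0.280 (the normal density 0.84 SD from the mean). A separate simulation of a 12-month contrast gave SDs of 0.149 (M = 10) and 0.066 (M = 50):
- M = 10: 1.128 x 0.149 = 0.168, so 2.0 % under the null and 4.7 % at 80 % power.
- M = 50: 1.128 x 0.066 = 0.074, so 0.9 % and 2.1 %.

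**The case against.** The strongest reply is that nothing here is wrong. Ten imputations with standard pooling are valid, and how much Monte Carlo noise to accept is a matter of tolerance. Fifty imputations still leave a range that straddles 0.05. That stands, and it is why this is an improvement and not a fault.

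Second, the figures depend on which effect is tested. The sample size was set for the between-groups effect. Averaged over all three time points, that effect has an SD of only 0.06-0.07 with ten imputations, about what 50 would give for a 12-month contrast. A Sidak-corrected pairwise comparison among three arms also has its threshold near z = 2.39, not 1.96. This stands as a limit on scope: the larger figures belong to follow-up and change contrasts, where the effect of treatment would show.

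Third, the FMI is assumed. HbA1c comes from medical records, so a participant who stops returning questionnaires may still have a value. The range in step 4 covers this in part: at FMI 0.10 the interval 0.030-0.081 still crosses 0.05.

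A reader might go further and infer that ten imputations bias the result or inflate type I error, that a primary p-value is arbitrary between 0.024 and 0.097, or that the result could not be reproduced from the same data. None of these is supported. The pooling rules allow for a finite number of imputations. The range is a plus or minus 2 SD range for a result that sits exactly on the threshold. A recorded seed makes even ten imputations exactly repeatable, and an article's silence on the seed is detail commonly left to the analysis plan, so it is no finding.

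**Conclusion.** The point holds as a free improvement. The plan fixes a number that is adequate for validity but low for the missingness it expects. With an FMI of about 0.20, a 12-month or change contrast carries a seed-to-seed SD of about 0.15-0.18. A result centred on p = 0.05 can then fall anywhere from about 0.024 to 0.10 (up to 0.11 in the simulation) from imputation noise alone, against about 0.037-0.069 with 50 imputations. In practice the gain is small: roughly one to three fewer discordant verdicts per 100 trials.

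This rests on an FMI close to the attrition rate, dropout at random, the protocol's correlation of 0.70, and a contrast at or to follow-up. It does not extend to the group effect averaged over all three time points, where the noise is less than half as large.

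**What to change.** In Preliminary analyses, replace the 10 imputed datasets with at least 50, or 100 if run time allows, and set the seed in advance. A fixed seed alone would make the answer repeatable but would not reduce its dependence on the draw, so the number should rise as well. The cost is minutes of computing. Data collection, the sample size and the analysis model stay as they are.

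### At 10 % missing data or less the plan analyses one singly imputed dataset as if it were observed; depending on the unstated imputation model this understates standard errors or shrinks a real effect

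*Protocol article*

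**What the plan says.** The section Preliminary analyses of the protocol article chooses the method by the amount of missing data.

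- Upper branch: "If missing data analyses indicate large levels of missing data (>10 % on any variable), multiple imputation using SPSS Markov Chain Monte Carlo procedures" "will be implemented to produce 10 imputed datasets". Each dataset is analysed, and "thereafter standard multiple imputation procedures will be used to combine the multiple scalar and multivariate estimates quantities".
- Lower branch: "If missing data levels are lower, a single imputation procedure will be implemented, followed by standard analyses procedures".

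Combining rules are given for the upper branch only. For the lower branch the article names no type of single imputation, no imputation model and no variance correction. The section Main analyses then plans a 3 x 3 mixed ANCOVA for HbA1c, CHD risk and the secondary outcomes, to be replaced by multi-level modelling if the data meet criteria. The sensitivity analysis named there is a per-protocol repeat, which does not address imputation uncertainty.

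**The concern.** Standard software counts an imputed value as a measured one. After a single imputation the analysis therefore uses the full sample size and degrees of freedom, although part of the outcome was never seen. Less missing data makes this error smaller but does not remove it.

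The harm takes one of two forms.

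- If the imputation model contains arm, the estimate is unbiased under the assumptions below, but its standard error is too small and tests of the arm effect reject too often.
- If the model omits arm, or the overall mean is filled in, imputed participants carry no treatment difference. The null error rate holds, but a true difference is pulled towards zero.

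At stake are the nominal 5 % level in the first case and the size of the estimated effect in the second. The article already plans a method that avoids both, and stops using it below the threshold.

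**Working it through.** **Inputs from the article.** Three arms of 80 (240 in total). From Power calculation: "alpha = 0.05, power = 80 %, f = 0.20 and a correlation between measurement points of 0.70". Expected attrition is 20 %. Threshold 10 % and 10 imputations are from Preliminary analyses.

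**The plan's own figure.** The article gives no number for the imputation rule, but the sample size that supplies the inputs reproduces. For the between-subjects test with four points, lambda = f² × N × m / (1 + (m − 1) × rho) = 0.04 × 192 × 4 / (1 + 3 × 0.70) = 30.72 / 3.1 = 9.91. With 2 and 189 degrees of freedom the power is 80.5 %. The stated 192 holds, and 192 / 0.80 = 240.

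**Assumptions added here.** Outcomes missing completely at random, baseline complete, normal data with correlation 0.70 between any two time points, and several types of single imputation, because the article names none.

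**Step 1: closed form, one outcome, imputed within arm, no predictors.** Let m now be the missing fraction.

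- Stochastic imputation: true/reported variance = 1/(1 − m) + m. At m = 0.10 this is 1.211, so actual alpha = 2(1 − Φ(1.96/√1.211)) = 7.5 %. At m = 0.05 it is 1.103, giving 6.2 %.
- Deterministic imputation: reported/true SE = 1 − m, giving 7.8 % at m = 0.10 and 6.3 % at m = 0.05.

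This shows the mechanism. It is not the planned analysis.

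**Step 2: simulation, one follow-up, ANCOVA on arm and baseline, arm in the imputation model, no true effect (10,000 runs; 3,000 for multiple imputation).**

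- 5 % missing: reported/true SE about 0.94; pairwise error 6.5-6.6 %, three-arm test 6.8-7.0 %.
- 10 % missing: SE ratio 0.89 (regression) and 0.90 (stochastic); pairwise error 8.0 % and 7.7 %, three-arm test 9.2 % and 8.3 %.
- Multiple imputation with 10 datasets and Rubin's rules: pairwise error 5.0 % at 5 % missing and 5.6 % at 10 % (Monte Carlo error about 0.4 points), which is about nominal.

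**Step 3: simulation, three time points, the same participants missing at 6 and 12 months (5,000 runs, Monte Carlo error 0.3-0.4 points).** Rejection rates of the three-arm test under no effect, at 10 % missing:

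| Imputation | 12-month ANCOVA | Averaged follow-up ANCOVA | Between-group, averaged over three points |
|---|---|---|---|
| Arm included, regression | 8.9 % | 8.9 % | 5.7 % |
| Arm included, stochastic | 8.3 % | 8.2 % | 5.7 % |
| Arm omitted, regression | 5.2 % | 5.1 % | 5.0 % |
| Arm omitted, stochastic | 4.8 % | 5.0 % | 5.1 % |
| Overall mean | 5.2 % | 4.9 % | 5.0 % |

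At 5 % missing, the baseline-adjusted tests with arm included give 6.5-6.7 %, and the between-group test over three points gives 5.6 %.

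A further simulation of the three-point structure (6,000 runs, imputing from arm and earlier values) gave 9.3-10.4 % for the group-by-time test at 10 % missing and 6.7-7.0 % at 5 %.

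**Step 4: a true difference of 0.40 SD in one arm (2,500 runs).** With arm in the imputation model the mean 12-month estimate is 0.40. With arm omitted, or the mean imputed, it is 0.36 at 10 % missing and 0.38 at 5 %. The loss is about the missing fraction: 0.40 × (1 − 0.10) = 0.36. On the plan's scale, a 6.25 % change would appear as about 6.25 × 0.90 = 5.6 %.

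**The case against.** The strongest objection is that this branch may never be used. The plan expects 20 % attrition, a single variable above 10 % triggers multiple imputation, and there are many questionnaire scales at four time points. On the plain reading multiple imputation is the likelier branch. This stands and limits the weight of the point. It does not make the lower branch sound: 20 % is a planning figure, and the text does not say whether the threshold is applied to the whole dataset or variable by variable.

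A reader might infer that the primary p-value will always be too small, with 7.5-7.8 % as its general error rate. The document does not support that. Those figures come from the closed form for one outcome imputed within arm. With arm omitted or the mean imputed, the null error rate stays near 5 %. The between-group test averaged over time, which is the kind of test the power calculation uses, stays at 5-6 % even with arm included.

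A reader might also infer that multiple imputation is switched off precisely for the record-based primary outcomes, or that the threshold lets the analyst choose a favourable result. The first needs a variable-by-variable trigger and a missingness figure for HbA1c, and the article gives neither. The second does not follow: the threshold is prespecified, depends on amounts of missing data rather than on effects, and is applied by an analyst blinded to allocation.

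The imputation model may be set out in a fuller plan, and its absence from the article is not the complaint. The article does fix single imputation followed by uncorrected analysis. The possible move to multi-level modelling does not cure this, because imputation comes first and no exception is made for that model.

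**Conclusion.** The point holds with modest weight. Whenever the lower branch applies, imputed values are analysed as observed. If arm is in the imputation model, baseline-adjusted three-arm tests run at about 8-9 % at 10 % missing and 6-7 % at 5 % missing, with the reported SE understated by up to about 11 %; the between-group test averaged over all time points shows little inflation. If arm is omitted or the mean is imputed, the level holds but a real difference is attenuated by about the missing fraction. These figures rest on 80 per arm, correlation 0.70, complete baseline data and outcomes missing completely at random. Which form of harm would occur cannot be told from the article, and the expected attrition makes the other branch the more likely one.

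**What to change.** Delete the sentence on single imputation. Then either:

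- use the planned multiple imputation at any level of missingness, with arm, baseline and all time points in the imputation model and the combining rules already stated; or
- analyse all observed follow-up data with a likelihood-based mixed model and impute no outcomes.

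Either removes the need for the 10 % threshold. The cost is slightly more analysis work and slightly wider confidence intervals. In the one-follow-up simulation at 10 % missing, the mean SE was 0.1197 with multiple imputation, against 0.1129 (stochastic) and 0.1071 (regression) with single imputation, that is about 6 % and 12 % larger. It was practically the same as the complete-case value of 0.1192, so the extra width reflects the information actually observed.
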